## Abstract

**Introduction:**

Opioid assisted treatment (OAT) with buprenorphine (BUP) is front-line medical maintenance intervention for illicit and prescription opioid use disorder (OUD). In many clinics, opioid medication is dispensed for several days for self-administration. This provides flexibility to the patient but may compromise the effectiveness of OAT because of nonadherence or medication diversion. OAT can be delivered as an entirely supervised intervention, but many patients discontinue treatment under this arrangement and dispensing costs may be prohibitive. An alternative is to enable patients to receive take-home doses contingent on OAT adherence guided by a medication management framework using Therapeutic Drug Monitoring (TDM) alongside negative urine drug screens (UDS) to provide evidence of abstinence. TDM is recommended to monitor adherence with BUP but it has not been applied in OAT programs and evaluation research to date.

**Methods:**

The Suboxone Treatment and Recovery Trial (STAR-T) is a single site, 16-week, parallel-group, randomised controlled trial. The aim of the study is to determine the effectiveness of a medication management framework including TDM and UDS to enable patients enrolled on outpatient OAT (with buprenorphine/naloxone [sublingual film formulation; BUP/NX-F; Suboxone™]) to receive stepped take-home doses. Following stabilisation during inpatient care, adult participants with illicit or prescription OUD were allocated (1:1) to receive (1) BUP/NX-F plus medication management for take-home doses based on TDM, UDS, and contingency management protocol (the experimental group) or (2) BUP/NX-F plus UDS only (treatment-as-usual, the control group). The primary outcome is the mean percentage of negative UDS over 16 weeks. The secondary outcome is treatment retention defined as completion of 16 weeks of OAT without interruption. There will be an exploratory analysis of the association between participant characteristics, clinical data, and outcomes.

**Conclusions:**

Providing BUP/NX-F take-home doses contingent on adherence and opioid abstinence may enable OAT to be delivered flexibly and effectively.

**Trial Registration:**

ISRCTN41645723 is retrospectively registered on 15/11/2015.

## 1. Introduction

 The annual mortality rate among the illicit opioid use population is 1%, a rate 10-fold greater than the general population [1]. The front-line, evidence-supported pharmacotherapy for opioid dependence [2] or opioid use disorder [3] (OUD herein) is oral methadone or sublingual tablet buprenorphine (BUP) maintenance [4]. On average, this opioid assisted therapy (OAT) is associated with clinically meaningful suppression of nonmedical opioid use and drug injection [5]. Studies have shown that patients who take buprenorphine/naloxone (BUP/NX) 80% of the time or more have a 10-fold increase in the odds of heroin abstinence [6] and those considered as compliant with BUP medication provide more opioid negative urine screens [7].

The effectiveness of OAT is hampered by treatment nonadherence and diversion, prescribing lower than the doses need [8], and also early discontinuation [9]. The medication dispensing policy may influence these negative outcomes. Medication can be administered either under direct supervision or flexibly, with the patient given the opportunity to receive “take home” doses for self-administration, contingent on medication adherence, and providing evidence of illicit opioid abstinence [10, 11]. A fixed policy of only dispensing medication under supervision substantially reduces the likelihood of medication diversion; but this may prove unpopular among patients and lead to drop out [9]. Medication dispensing costs may also be prohibitive for many clinical services [12]. Patients respond well to a medication management framework using flexible dosing and behavioural reinforcement (contingency management [CM] is associated with good adherence [11]), although there remains a risk of medication diversion [9]. The current evidence shows no difference between the fixed and the flexible OAT prescribing practice in reducing opioid use or enhancing retention in treatment. This evidence however was judged to be of low quality [13].

Several patient characteristics are associated with sub-optimal OAT response. Younger patients [14] and those with unstable housing [15] tend to have a higher risk of treatment discontinuation. Co-occurring mental health disorders have a prevalence of 40 to 55% in this clinical population [16] and may be associated with compromised treatment response [17]. In particular, depression and anxiety disorders are often reported to predict treatment discontinuation [18] and heroin use [18]. Personality disorders (particularly borderline personality disorder) are associated with poor prognosis of substance use treatment [19]). An impulsive personality trait has been observed to predict noncompletion of SUD treatment [20]. Sleep disorders are associated with day-time dysfunction in the heroin using population which may compromise patient engagement in treatment [21].

Buprenorphine and naloxone (BUP/NX; ratio 4:1; and a sublingual film formulation [Suboxone®; BUP/NX-F developed for rapid dissolution]) have been developed for maintenance OAT with the aim of suppressing the likelihood of illicit opioid injecting (because the opioid antagonist naloxone may cause opioid withdrawal) and maximising adherence (because BUP/NX-F is very hard to remove once placed under the tongue). In contrast to BUP mono therapy, there is evidence that these alternative formulations deliver further reduction in diversion [22]. A ‘pill or medication count' practice has also been recommended as part of the effort to increase medication adherence [23] but, to date, there are no reported randomised controlled trials.

Therapeutic Drug Monitoring (TDM) is a patient centered and precision medicine tool that involves quantitation and interpretation of medication blood concentrations with necessary dose adjustments to optimise treatment outcomes [24]. It has been applied in neuropsychiatry to enhance outcomes of antiepileptics [25], antipsychotics [26], and mood stabilisers [27] and for monitoring drug-drug interactions [28]. The potential value of TDM in OAT has been recognised as a monitor of compliance [24] yet there is no consensus or guidelines on how it should be clinically implemented and there have been no published clinical trials.

Against this background, the present study will determine the effectiveness of TDM, urine drug screens (UDS), and medication take-home dosing by CM. To our knowledge, there have been no trials that use these adjunctive elements in OAT. In this protocol paper, we describe the design, methods, procedures, and strengths and limitations for a randomised controlled trial to determine the clinical effectiveness of an adjunctive medication management protocol for OAT with BUP/NX-F.

## 2. Methods

### 2.1. Study Design, Population, and Setting

The Suboxone Treatment and Recovery Trial (STAR-T) is a single centre, 16-week outpatient intervention, two-arm, pragmatic, phase IV randomised controlled trial of OAT and adjunctive TDM for OUD. The study population is adults (≥ 18 years) with current OUD.

The study setting is the specialist OUD treatment and care programme operated by National Rehabilitation Centre (NRC), Abu Dhabi, United Arab Emirates (UAE; www.nrc.ae). In the UAE, use and combination use of heroin, morphine, and illicit tramadol are the most prevalent [29, 30]. The NRC treatment programme includes an inpatient unit for assessment and management of medical and mental health comorbidities with (poly) substance and alcohol use disorders [29–31]. In 2002, the NRC introduced OAT with BUP with induction and stabilisation procedures conducted in the inpatient unit. However, following concerns about medication diversion in 2011, the NRC suspended all new admissions to OAT pending the development and findings from the present study.

Following a standard of care protocol for OAT, all participants will first complete inpatient care (up to four weeks) to achieve medically supervised withdrawal and stabilisation on BUP/NX-F and to estimate the BUP Elimination Rate (EL.R). After study enrolment and prior to discharge, participants will be randomly allocated (1:1: using an online randomisation service [32] with no stratification) to an experimental group (that immediately received 16 weeks of outpatient BUP/NX-F maintenance, standard case management, and manualised adjunctive medication management with TDM monitoring and CM) or to a treatment-as-usual, control group (that immediately received BUP/NX-F and standard case management and usual medication management only). Using ongoing medication management, TDM, and CM protocol, participants in the experimental group will be able to receive up to four weeks of medication on a take-home basis. All participants will continue to receive ongoing treatment after 16 weeks as usual.

The trial will follow the ethical principles of the World Medical Association's Declaration of Helsinki for research involving human subjects and is registered with the ISRCTN (number: 41645723). The study will adhere to the medical research guidelines of the Department of Health of Abu Dhabi [33] and the CONSORT guideline extension for pragmatic randomised controlled trials [34]. Good clinical practice training will be provided in the UAE and in the United Kingdom by King's Health Partners Clinical Trials Office (https://www.khpcto.co.uk).

The study protocol, participant information sheet (describing the study rationale, design and procedures), participant consent form, and clinical research forms have been approved by the Institutional Review Board of the National Rehabilitation Centre, Abu Dhabi (number: NRC/2/2014; granted April 2014; first participant enrolled on 15.9.2014).

### 2.2. Study Aims

The primary aim of this pragmatic study is to determine if BUP/NX-F with adjunctive TDM is clinically superior to BUP/NX-F only in terms of reduced opioid use during outpatient treatment.

In addition to determining group differences on OAT retention, there are two exploratory secondary aims: (1) to determine if there are associations between participant demographics, two BUP parameters (elimination rate and dose), and opioid use and treatment retention; and (2) to determine if there are associations between patient psychosocial functioning and opioid use and treatment retention.

STAR-T also includes an exploratory health economic (cost-benefit and cost-effectiveness) evaluation. This component of the study will be described and reported separately.

### 2.3. Participant Eligibility and Enrolment Procedure

The participant inclusion and exclusion criteria for the study are summarised in Table 1. Screening of patients for study eligibility was carried at intake before admission to the inpatient detoxification unit.

### 2.4. Research Assessments

The following measures were recorded prior to randomisation (baseline), during the outpatient treatment phase (as shown in parentheses; see Table 2 for summary)

#### 2.4.1. Urine Drug Screen (with Confirmatory Testing; Baseline and Every Clinic Visit) and BUP Level Determination (See Section 2.7 for Frequency of Administration)

A 5-minute, point-of-care immunoassay UDS test will be used that is US FDA approved and Clinical Laboratory Improvement Amendments (CLIA) waived for the following drugs screen in urine: opioids (morphine for illicit heroin), propoxyphene, tramadol, oxycodone, benzodiazepines, tricyclic antidepressants, psychostimulants (d-amphetamine, methyl-amphetamine, MDMA, cocaine), cannabinoids, phencyclidine, and BUP. All urine samples were collected under supervision, and positive screens were sent for confirmatory analysis at the laboratory using Gas Chromatography Tandem Mass Spectrometry. BUP levels were detected and quantified by Liquid Chromatography Tandem Mass Spectrometry (Schimadzu Scientific Instruments) with a Raptor C18 analytical column (Restek Corporation; 9304A12).

#### 2.4.2. Clinical Opioid Withdrawal Scale (COWS [35]; See Table 2)

The COWS is an 11-item clinician-administered scale which assesses opioid withdrawal signs and symptoms (a higher score indicates more severe opioid withdrawal).

#### 2.4.3. Pupil Reflexes (PLA Inc. 2000; Neuroptics, https://neuroptics.com; See Table 2)

A hand-held camera captures three pupil reflexes [36]: (1) maximum pupil diameter reading before exposure to light (before contraction). (2) minimum pupil diameter reading after exposure to light (after contraction), and (3) maximum and average constriction velocity, dilation velocity, and time to 75% recovery of pupil diameter.

#### 2.4.4. Patient Health Questionnaire (PHQ-9 [37]; See Table 2 for Frequency of Administration)

The PHQ-9 is as a validated, self-administered 9-item scale recording frequency of depression-related symptoms according to the DSM-IV depression criteria using responses over the past two weeks. The PHQ-9 screens for mild, moderate, moderately severe, and severe depression at cut-offs of 5, 10, 15, and 20, respectively. A validated Arabic version downloaded from the PHQ Screeners webpage [www.phqscreeners.com] was used in the present study.

#### 2.4.5. Generalised Anxiety Disorder (GAD-7 [38]; See Table 2 for Frequency of Administration)

The GAD-7 is a validated, self-administered 7-item scale recording frequency of anxiety-related symptoms according to the DSM-IV anxiety criteria using responses over the past two weeks. The GAD-7 screens for mild, moderate, and severe anxiety at cut-offs of 5, 10, and 15, respectively. A validated Arabic version downloaded from the PHQ Screeners webpage [www.phqscreeners.com] was used in the present study.

#### 2.4.6. Barratt Impulsiveness Scale (BIS-11 [39]; See Table 2 for Frequency of Administration)

The BIS-11 is a validated, 30-item self-administered questionnaire that assesses three impulsiveness subtraits: nonplanning, motor, and attention. Items are rated over a four-point scale (“never” to always; scored 0 to 4 total score range: 0 to 120). A higher score indicates higher trait impulsiveness.

#### 2.4.7. Personality Disorder Screener (PDS [40]; See Table 2 for Frequency of Administration)

The PDS is a validated, clinician-administered 34-item “true”, “false”, or “do not know” checklist. Scoring follows the ICD-10 criteria to screen for three clusters of personality disorders: Cluster A (Odd or Eccentric), Cluster B (Borderline Personality), and Cluster C (Anxious Personality).

#### 2.4.8. Addiction Severity Index (ASI-Lite Version [41]; See Table 2 for Frequency of Administration)

The ASI-lite is a validated, semistructured interviewer administered outcome evaluation instrument that assesses seven addiction severity domains over the past 30 days (medical and employment and social status; alcohol use; drug use; family; legal; and mental health). The tool generates a composite score for each domain (ranging from “0 to 1”), with higher scores indicating higher problem severity.

#### 2.4.9. Work and Social Adjustment Scale (WSAS [42]; See Table 2 for Frequency of Administration) 

The WSAS is a validated, 5-item self-reported scale that measures perceived personal, social, and occupational impairment caused by a clinical problem (OUD in the present study). Each item is rated using an 8-point scale (“0” [no impairment] to “8” [full impairment]; total score range: 0 to 40). A score of “10 to 20” indicates significant impairment and a score of “21 to 40” reflects severe impairment.

#### 2.4.10. Pittsburgh Sleep Quality Index (PSQI [43]; See Table 2 for Frequency of Administration)

The PSQI is a validated, self-administered tool that evaluates sleep quality across seven categories with items rated on a 3-point scale (total score 0 to 27). A higher score reflects worse sleep quality and the cut-off score for sleep disorders is “5”. The published Arabic version by Suleiman and colleagues in 2010 [44] will be utilised.

#### 2.4.11. Minnesota Cocaine Craving Scale (MCCS [45]; See Table 2 for Frequency of Administration)

The MCCS is a validated, 5-item scale measuring the following aspects craving: intensity, duration, frequency, change from last week/day, and how the medication has helped. The MCCS was adapted to record “opioids” (MOCS) for the present study.

### 2.5. Patient Education and Medication Management Materials

The following materials were developed to support trial implementation and fidelity: 

*(1) Medication Education Leaflet*. An educational material on how to use BUP/NX-F was developed for patient medication education [46] and following the BUP clinical practice published by the US Department of Health and Human Services-Substance Abuse and Mental Health Services Administration [37]; 

*(2) Emergency Card*. As a safety measure, a wallet-size hard card was developed for health care professionals who attend participants in the state of emergency specifying the prescription of BUP/NX-F; 

*(3) Patient Diary/“Recovery Passport”*. A passport-sized diary was developed based on the patient health engagement model [47], self-management, and principles of CM to include material on self-assessment, a log of BUP/NX-F dosing (validated by the participant and a family member), and a log of clinic visits for UDS and results; 

*(4) Patient Counselling Checklist*. A 19-item checklist is developed to guide medication counselling [48]; and 

*(5) Medication Management Manual*. A manual was developed to structure the medication management sessions for the experimental group. This was based on material developed for US trials of alcohol [49] and opioid pharmacotherapy [50] and included monitoring forms to individualise interventions and text to guide the clinician's interactions with the patient.

### 2.6. Procedures

#### 2.6.1. Buprenorphine/Naloxone Induction and Stabilisation

On the first day of admission to the inpatient unit, participants' pupil reflexes will be measured to provide a baseline for monitoring craving and medication response. Then, at the first sign of withdrawal, a three-day or five-day supervised BUP/NX-F induction will commence for individuals with morphine/heroin use disorder or pharmaceutical OUD, respectively. The longer induction period for the latter group reflects the relatively longer half-life of these products compared to heroin.

BUP/NX-F will be initiated at a dose of 2 to 4 mg will be used for those with a COWS score of <10. The participant will be closely observed during the first 4 hours to signs of precipitated withdrawal, together with regular pupil reflex monitoring and COWS assessments. The participant's dose will be increased by 2 to 4 mg to a maximum of 8 mg in the first 24 hours. On the second day of induction, the dose will be increased by 4 to 6 mg every 4 to 6 hours to a maximum of 24 mg per day.

With an achieved COWS score of <5, the participant will be transferred to an “early recovery unit” a step-down phase to achieve BUP/NX-F stabilisation. Each participant will be assigned to a personalised dosing schedule (i.e., daily, alternate-day [Alt-D] or thrice-weekly [TIW]) followed by further dose adjustment as required. Those who continue to report distressing opioid craving or do not tolerate their dosing schedule satisfactorily will be transferred to another (usually more frequent) schedule. The published correlation of patient characteristics and BUP/BUP/NX maintenance doses [51, 52] will serve as the theoretical basis for this regimen and the daily, or the total 24-hour dose, required to achieve a COWS scores <5 will be used as the reference for estimating non-daily doses.

The Alt-D schedule will be a 3 × 48-hour dose and 1 × 24-hour dose. The TIW schedule will be a 2 × 48-hour dose and 1 × 72-hour dose (calculated as 3 × 24-hour dose at a maximum of 32 mg) [53, 54]. Clinical determination of the dosing schedule was informed by illicit injecting status (i.e., participants injected street heroin/morphine will receive daily doses and noninjected heroin and morphine users received alternate daily doses) while prescription opioid users (nonpolysubstance users) will receive TIW doses. Additionally, participants with severe psychiatric comorbidity, polysubstance use, or a body mass index (BMI) of ≥30 will be placed on the next higher frequency schedule (e.g., from TIW to ALT-D). Fine dose adjustments will be guided by self-report participant comfort, sleeping, craving, and pupil reflexes. Participants continuing to observe craving and or signs of withdrawal will be transferred to the next frequent dosing schedule towards the daily schedule as illustrated by Figure 1.

#### 2.6.2. Estimating the Buprenorphine Elimination Rate Constant

Maintenance of a BUP/NX-F dose without change for two weeks will be taken to indicate that a BUP steady state concentration (SSC) [55] has been achieved for participants receiving a daily or Alt-D dosing schedule. A longer period of 21 days (or an equivalent of 9 doses) will be needed to achieve SSC for participants assigned to TIW. Then, applying the function for first order kinetics (Figure S1), the BUP EL.R will be estimated by

(1) examination of the peak BUP plasma concentration measured 40 minutes after the dose on day 19 and day 22 [peak concentration, C-max]; and

(2) examination of BUP trough levels measured 30 minutes prior administering BUP/NX-F on day 21 and day 24 (trough concentrations, C-min). The replication of two trough concentrations will be taken to confirm that a SSC has been achieved. It is possible that additional samples will need to be drawn until SSC is confirmed. The reliability of the first order pharmacokinetic (PK) model to accurately predict BUP levels will be evaluated in the first 15 participants recruited to the study in the form of an internal pilot study for TDM. After confirming the reliability of the PK model in all 15 participants, the study will proceed to definite recruitment and results from the pilot will be included in the study analysis. Details of the laboratory assay and clinical procedures for this step will be presented separately.

#### 2.6.3. Interventions for Experimental Group

In week one of outpatient care, participants allocated to the BUP/NX-F and TDM (experimental) group will receive directly supervised doses according to their dosing schedule. Participants are required to randomly provide a minimum of three negative UDS during these visits on a random basis. If the participant is able to meet this this requirement, a CM protocol will enable them to receive a one-week prescription of medication for self-administration at home. On return for their prescription to be refilled, a negative UDS will enable the participant to receive a two-week prescription and then a three-week prescription. On the other hand, if the participant is not able to meet the initial requirement (i.e., they fail to attend all appointments or provide at least three negative UDS) they will receive supervised dosing for another week (five days for daily dosing schedule and two days of take home for the weekend). At any point, a positive UDS will either hold the participants on five-day supervised dosing or step them down to this arrangement from the two-week or three-week dosing arrangement.

For the TDM element, after the participant has been able to earn a two-week take-home prescription, a blood sample will be collected during a clinic visit for laboratory to measurement of BUP level labelled the “observed concentration”. On the sample collection day, participants will be strictly advised not to take their BUP/NX-F dose and the quantity of medication dispensed will be accounted for by the pharmacy. The exact time of blood sample collection, the time of the last BUP/NX-F dose taken/administered, and the established BUP EL.R will be applied in the function of first order kinetics (Figure S1) to predict the participant's concentration labelled as “predicted concentration” of BUP. If the observed and predicted concentration values do not differ by more than 15%, the participant will be classified “adherent”. Participants who are adherent will be stepped up to a three-week take-home prescription. All nonadherent participants will be stepped down to a one-week take-home prescription.

On a random basis, all participants who attain the three-week take-home prescription will be invited to visit the clinic between scheduled visits to give a blood sample for BUP testing and also to take a UDS. Nonadherent or nonabstinent participants will be stepped down to two-week take-home prescription while adherent and abstinent participants will receive a four-week take-home prescription at the next scheduled visit (the maximum permitted for the trial). During outpatient treatment, participants who are assessed as both nonadherent and nonabstinent will be reset to supervised dosing.

During the first week of outpatient care, two medication management foundation sessions will be scheduled to help participants (1) understand the importance of taking BUP/NX-F as prescribed, (2) become aware of BUP/NX-F mechanism of action and ways to monitor withdrawal signs and adverse events, (3) recognise and cope with cravings, and (4) build and sustain motivation for abstinence. Then, medication management maintenance sessions will be offered in response to the following four participant conditions: 

*Abstinent and Adherent*. Discussion is held to reinforce and motivate continued abstinence and medication adherence. Prescription for take-home doses will be extended step-wise to a maximum of four weeks. 

*Abstinent but Nonadherent*. Discussion is held to reinforce and motivate continued abstinence, remind the participants about the value of adherence, identify the source of nonadherence and strategies to improve adherence. A follow-up call on the agreed tasks will be arranged and prescription for take-home doses will be stepped down by one level. 

*Nonabstinent but Adherent*. Discussion is held to reinforce and motivate medication adherence and remind participants about the value of abstinence. The context and triggers for using will be assessed and relapse prevention strategies discussed. Additionally, comorbid conditions and social situations will be evaluated with referral to ancillary services. The prescription for take-home doses will be stepped down by one level. 

*Nonabstinent and Nonadherent*. Functional assessment of relapse/lapse will be performed, with referral to an appropriate service if co-occurring conditions were identified. Engagement of family members and close network will be sought to encourage retention. The participant will be transferred to five-day supervised BUP/NX-F dosing.

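### Section 2.6.3 gives two incompatible consequences of a positive UDS for adherent experimental-arm participants on a two- or three-week take-home supply

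*Protocol article*

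**What the plan says.** All the text at issue is in section 2.6.3 (Interventions for Experimental Group) of the protocol article.

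- **Positive-screen rule** (first paragraph). "At any point, a positive UDS will either hold the participants on five-day supervised dosing or step them down to this arrangement". The sentence then names the levels it reaches: "step them down to this arrangement from the two-week or three-week dosing arrangement".
- **Random check on the three-week level.** Participants are called in between visits for a BUP sample and a UDS. "Nonadherent or nonabstinent participants will be stepped down to two-week take-home prescription".
- **One-level rule.** Under the condition of being nonabstinent but adherent: "The prescription for take-home doses will be stepped down by one level".
- **Reset rule.** During outpatient treatment, "participants who are assessed as both nonadherent and nonabstinent will be reset to supervised dosing".

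Two other places matter. The heading of section 2.4.1 sets UDS at baseline and at every clinic visit. Section 2.7.1 makes the primary outcome the count of negative opioid screens over 16 weeks; the abstract gives it as a mean percentage.

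**The concern.** The stepped contingency is a large part of what the experimental arm adds to usual treatment. Table 3 lists stepped take-home doses as present in one arm and absent in the other. If the text gives two answers to a positive screen, a clinician who follows one departs from the other, and delivery can vary between staff or over time with no breach of protocol.

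Three things depend on which answer is used:

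- **Fidelity.** There is no single stated consequence against which to judge what was delivered after a positive screen.
- **The primary outcome.** Screens are taken at clinic visits and supervised dosing brings more visits. The rule applied therefore changes how many screens a participant contributes. That matters for a count directly and for a percentage through its denominator.
- **Unsupervised supply.** The amount of medication held at home after a positive screen differs between the rules.

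**Working it through.** No sample-size, power or event figure enters, and the plan states no figure to reproduce. The check applies each rule to a participant who is adherent by BUP level and gives a positive UDS, at every step of the ladder.

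| Current level | Positive-screen rule | One-level rule | Compatible? |
|---|---|---|---|
| Supervised | stays supervised | no lower level | yes |
| One week | supervised (level not named, but any point is covered) | supervised | yes |
| Two weeks | supervised (two levels down) | one week (one level down) | **no** |
| Three weeks | supervised (three levels down) | two weeks (one level down) | **no** |
| Four weeks | not named; supervised if read literally | three weeks | **no**, if read literally |

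**Can the first rule be confined to the period before BUP monitoring?** No. It applies at any point and names the three-week level, which the same section reaches through a BUP result: "Participants who are adherent will be stepped up to a three-week take-home prescription".

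**Can the first rule simply override the second?** Not without emptying it. A nonabstinent but adherent participant on two or three weeks would then go to supervised dosing, exactly as one who is both nonabstinent and nonadherent. The separate take-home consequence for the adherent group would mean nothing at those levels.

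**Other cases.** A participant who is nonadherent only goes from two weeks to one, or from three to two, which agrees with the one-level rule. A participant who fails on both counts goes to supervised dosing under the positive-screen rule and the reset rule alike. The random-check sentence joins its conditions with 'or', so it can be read to send that participant to two weeks instead. The main conflict is confined to positive screens in adherent participants.

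**Illustration of size.** Take an adherent participant on three weeks with one positive UDS. The assumptions, none of which the article states for this situation, are:

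1. All later results are satisfactory, and BUP results are ready at the visit.
2. The week-one requirement (one supervised week, at least three negative screens) also governs re-earning.
3. A supervised week yields 3 to 5 screens: the stated minimum, up to one per supervised day.
4. Under the one-level rule, one random check falls within the four weeks.

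- Time to regain three weeks, positive-screen rule: 1 (supervised) + 1 (one-week supply) + 2 (two-week supply) = 4 weeks.
- Time to regain three weeks, one-level rule: 2 weeks (one two-week supply).
- Screens in the next four weeks, positive-screen rule: 3 + 1 + 1 = 5 up to 5 + 1 + 1 = 7.
- Screens in the next four weeks, one-level rule: 1 (refill visit) + 1 (random check) = 2.
- Difference: 5 − 2 = 3 up to 7 − 2 = 5 screens.
- Supply held straight after the positive screen: two weekend days for a daily-schedule participant (if the weekend arrangement described for a repeated supervised week applies) against 14 days.

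**The case against.** The best defence is that the rules serve different visits. The four conditions in section 2.6.3 need both a UDS and a BUP result. A blood sample is described only after the two-week supply is earned and at the random check on three weeks. At a visit with a UDS alone there is no adherence class, so the positive-screen rule could govern those visits and the one-level rule the rest.

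This is a sensible way to repair the text, but the text does not say it. The positive-screen rule covers any point without exception. The split would also leave a gap in practice: the UDS is a five-minute test (section 2.4.1), while the Discussion acknowledges an extended turn-around for BUP levels. A positive screen may therefore have to be acted on before the BUP result that decides which rule applies.

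A second defence is that the medication management manual, which is not shown, may contain an operational step table. It may. That limits what can be said about conduct, but the article does not merely omit a detail here: it states two rules that disagree.

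The illustrative counts are also open to challenge. Re-earning after a step-down may not follow the week-one requirement, and delayed BUP results would alter the timings. That stands, and the counts should not be read as figures from the plan.

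**Conclusion.** The text is wrong as written. For experimental-arm participants who are adherent by BUP level and give a positive UDS on a two- or three-week supply, section 2.6.3 requires both a return to five-day supervised dosing and a step down of one level. The same holds at four weeks if the first rule is taken literally. This conclusion rests on the wording alone.

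For a single event at three weeks, the rules could differ by about 3 to 5 screens over four weeks under the assumptions listed. The net effect on the trial cannot be computed, because the article gives no rates of positive screens, nonadherence or missed visits.

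A reader might infer more than the documents support:

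- **That the rules are opposite.** Both step the participant down, by different amounts, and they agree at the two lowest levels.
- **That two different interventions were delivered.** Nothing shows that staff applied both rules.
- **That the 5% audit in section 3 has no standard.** It covers material recorded in the medication management sessions, and the manual that structures those sessions is not shown.
- **That a UDS alone earns the three-week supply**, because "a negative UDS will enable the participant to receive a two-week prescription and then a three-week prescription". The next paragraph adds the BUP check to that ladder, and Table 3 makes take-home doses in this arm contingent on UDS and TDM together. The sentence is reasonably read as completed by them.

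**What to change.** 1. **Reconcile the passages.** The sponsor and clinical investigators should replace the competing sentences with one table: current level × UDS result × BUP-level result gives next level. It should include a row for no BUP result available, name the four-week level, and settle a participant who fails on both counts at the three-week random check. The protocol and the manual should carry the same table. Which rule stands is a clinical decision and is not proposed here.
2. **Document what was done.** Recruitment began in September 2014 and section 4 describes analysis as in progress. For participants already treated, code from existing visit and pharmacy records which consequence was applied at each positive UDS, by level, and report the counts. If only one rule was used, the counts will show it.

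The cost is a protocol clarification, a manual page and retrospective coding of existing records. No new data collection is needed, provided those records show the supply level before and after each positive screen.
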